### 8.3 ADVERSE EVENTS AND SERIOUS ADVERSE EVENTS

*Leave blank. Text should be included under the relevant subheadings below.*

#### 8.3.1 DEFINITION OF ADVERSE EVENTS (AE)

The FDA definition of an Adverse event is any untoward medical occurrence associated with the use of an intervention in humans, whether or not considered intervention-related (21 CFR 312.32 (a)). Additionally, the study team defines an adverse event as any unfavorable medical occurrence in a subject related to research participation, including signs, symptoms, or diseases.

The DRES-POCAI study has a protocol that describes the procedures for identifying, monitoring, and reporting all AE, including both serious and non-serious events, and UP involving risk to participants or others. There are different categories of AE and UP that may occur with individuals who present at SYHealth enrollment sites with the intention of participating in the research study (**SOP Adverse Events and Unanticipated Problems**).

- **Potential Risk (PR):** The possibility of harm or negative outcomes that participants might experience as a direct or indirect result of their involvement in the study. These risks can be physical, psychological, or socioeconomic in nature.
- **Adverse Event (AE):** Any unfavorable medical occurrence in a subject related to research participation, including signs, symptoms, or diseases.
- **Serious Adverse Event (SAE):** An adverse event with severe outcomes like death, life-threatening situations, extended hospitalization, persistent disability, or those needed medical intervention to prevent such outcomes.
- **Unanticipated Problem (UP):** An adverse event unexpected in the research context, possible related to participation, and indicating higher risks than previously known.

---

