### 8.3.2 DEFINITION OF SERIOUS ADVERSE EVENTS (SAE)

An adverse event (AE) or suspected adverse reaction is considered "serious" if, in the view of either the investigator or sponsor, it results in any of the following outcomes: death, a life-threatening adverse event, inpatient hospitalization or prolongation of existing hospitalization, a persistent or significant incapacity or substantial disruption of the ability to conduct normal life functions, or a congenital anomaly/birth defect. Important medical events that may not result in death, be life-threatening, or require hospitalization may be considered serious when, based upon appropriate medical judgment, they may jeopardize the participant and may require medical or surgical intervention to prevent one of the outcomes listed in this definition. Examples of such medical events include allergic bronchospasm requiring intensive treatment in an emergency room or at home, blood dyscrasias or convulsions that do not result in inpatient hospitalization, or the development of drug dependency or drug abuse.

---

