#### 8.3.3.2 RELATIONSHIP TO STUDY INTERVENTION

All AEs must have their relationship to study intervention assessed by the team member who conducted the intervention activities with the participant based on temporal relationship and staff judgment. The

degree of certainty about causality will be graded using the categories below. In a clinical trial, the study product must always be suspect.

- **Related** – The AE is known to occur with the study intervention, there is a reasonable possibility that the study intervention caused the AE, or there is a temporal relationship between the study intervention and event. Reasonable possibility means that there is evidence to suggest a causal relationship between the study intervention and the AE.
- **Not Related** – There is not a reasonable possibility that the administration of the study intervention caused the event, there is no temporal relationship between the study intervention and event onset, or an alternate etiology has been established.

---

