#### 8.3.4. TIME PERIOD AND FREQUENCY FOR EVENT ASSESSMENT AND FOLLOW-UP

The occurrence of an AE or SAE may come to the attention of study staff during study visits and interviews of a study participant or upon review by a study monitor. All AEs that do not meet the criteria for SAEs will be captured on the appropriate case report form (CRF). Information to be collected includes event description, time of onset, staff or expert's assessment of severity, relationship to study intervention (assessed only by those with the training and authority to make a decision), and time of resolution/stabilization of the event. All AEs occurring while on study must be documented appropriately regardless of relationship. The study manager will record all reportable events with start dates occurring any time after informed consent is obtained until 7 (for non-serious AEs) or 30 days (for SAEs) after the last day of study participation. At each study visit, the PI will inquire about the occurrence of AE/SAEs since the last visit. All AEs will be followed to adequate resolution (**SOP Adverse Events and Unanticipated Problems**).

The Point of Care Artificial Intelligence DR screening procedure presents minimal risk to participants and the RAs will emphasize that it is specifically for diabetic retinopathy, not a substitute for a full eye examination. Examples of anticipated AE and AE response.

- If a participant shows signs of depression, stress, or anxiety, the staff will approach each situation with caution. This includes being attentive during consent, baseline survey, or screening processes that might emotionally affect the participant. In such cases, the staff will offer the participant a break, provide tissues or water, and inform them of the remaining tasks, asking if they would like to continue or need a break.
- If a participant shows signs of syncope or near syncope, the staff will assist the participant to either sit with their head between their knees or recline, if possible, use smelling salts, if necessary, provide a basin and towel if the participant is feeling nauseous, and ensure the participant remains seated until recovery. The study coordinator will be notified and decide whether the participant should continue with study activities or if medical intervention is needed.

---

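### Section 8.3.1 limits adverse events to those related to participation while 8.3.4 wants them documented regardless of relationship, and 8.3.1 and 8.3.2 define serious events differently

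*Combined protocol and SAP*

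**What the plan says.** Section 8.3.1 of the protocol gives two definitions of an adverse event in consecutive sentences. The first is the regulatory one: "any untoward medical occurrence associated with the use of an intervention in humans, whether or not considered intervention-related". The second is the study's own: "the study team defines an adverse event as any unfavorable medical occurrence in a subject related to research participation". The bulleted categories that follow use only the second, describing an adverse event as "any unfavorable medical occurrence in a subject related to research participation, including signs, symptoms, or diseases".

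Section 8.3.4 sets the capture rule: "All AEs occurring while on study must be documented appropriately regardless of relationship". It lists relationship to the intervention as one of the items recorded for each event. Section 8.3.3.2 supplies two grades, related and not related, and says the grade is "assessed by the team member who conducted the intervention activities with the participant". Section 8.3.4 reserves that judgement for people with suitable training and authority.

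For serious events, the 8.3.1 bullet gives examples: "death, life-threatening situations, extended hospitalization, persistent disability", and events needing intervention to prevent such outcomes. Section 8.3.2, which is headed as the definition, includes "inpatient hospitalization or prolongation of existing hospitalization", congenital anomaly, and important medical events by judgement.

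The planned safety output is descriptive. Protocol 9.4.4 and the SAP's paragraph on safety analysis and data monitoring foresee no safety endpoint. All documented adverse events go into the final report and, under the SAP, to the data safety monitoring committee.

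**The concern.** A definition decides what enters the record; a causality grade describes what is already there. The study's own definition makes relatedness a condition of entry. A member of staff who follows the bullet could leave out an illness judged unconnected with the study, while a colleague who follows 8.3.4 would record it.

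The effect carries into serious events, because both sections define a serious event as a kind of adverse event. Under the narrow wording, a death or admission judged unrelated to participation is not an adverse event and so cannot be a serious one.

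The judgement would be made by unblinded staff (SAP, Blinding). Under section 4.4 the intervention screening takes place at the study visit, while usual-care screening takes place on another day and at another location. A filter based on perceived relatedness could therefore act differently in the two arms. Section 10.1.5 has the committee review safety data by arm. With no safety endpoint, the listing is the trial's main safety record, and an event screened out at entry cannot be recovered from it.

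**Working it through.** The documents give no event rate or safety figure to reproduce, so the check is a comparison of texts.

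1. *An unrelated illness during follow-up.* Under the first sentence of 8.3.1 ("whether or not considered intervention-related") relationship to the intervention does not exclude it. Under the study sentence and the bullet it is not an adverse event. Section 8.3.4 points to the broad reading but does not settle the matter: its rule applies to all adverse events, and 8.3.1 decides what those are.

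2. *A short first admission.* Under 8.3.2 it is serious. Under the 8.3.1 bullet, which names extended hospitalization within an open list of examples, its status is unclear. Congenital anomaly appears only in 8.3.2.

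3. *What seriousness changes.* Under 8.3.4, non-serious events are recorded until 7 days after the last day of participation and serious events until 30 days after. An admission between day 8 and day 30 is thus inside the window if serious and outside it if not. Section 8.3.5 also makes seriousness a trigger for immediate reporting, though not the only one.

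4. *Who grades relatedness.* Section 8.3.3.2 names the person who ran the activity; 8.3.4 names those with training and authority. The two agree only if the first person always belongs to the second group, which the protocol does not state.

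5. *A side effect of the broad definition.* Section 4.4 anticipates about 6 months of participation in usual care and about 12 in the intervention arm. Expected unrelated events = participants × years × rate. With 424 per arm and an **assumed** rate of 5% to 15% per person-year:
   - intervention: 424 × 1.0 × 0.05 = 21.2, to 424 × 1.0 × 0.15 = 63.6;
   - usual care: 424 × 0.5 × 0.05 = 10.6, to 424 × 0.5 × 0.15 = 31.8.

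   That is about 21 to 64 events against 11 to 32, a ratio of 2 from time on study alone. This ignores the 7- or 30-day tail and assumes that everyone completes the planned period.

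**The case against.** Several points on the other side are sound.

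- **The study sentence is introduced as an addition.** It could be meant to extend coverage to consent and surveys. That reading is possible for the sentence, but it does not explain the bullet, which stands alone and carries only the narrow wording.
- **The capture rule in 8.3.4 is explicit.** It also has the investigator ask about events at each visit, so many staff would record broadly. This lowers the risk without removing the contradiction. A reader might infer that unrelated events will never reach the committee. The documents do not support that; it would require 8.3.4 and the first sentence of 8.3.1 to be ignored.
- **The not-related grade still has a use.** A reader might infer that under the narrow definition this grade could never be given, so that its share is zero by construction. That does not follow. The definition refers to participation in the research, whereas 8.3.3.2 grades relation to the intervention. Distress during consent or the baseline survey, which 8.3.4 itself anticipates, can be related to the first and not to the second.
- **The serious-event bullet is an open list.** It does not say that a short admission is not serious; it only leaves this unclear.
- **Other routes exist.** Section 8.3.5 sends incidents as well as adverse events to the committee within 48 hours and extends immediate reporting to injuries and to incidents that incur medical costs. Section 8.3.6 sends all emergencies to the committee and the ethics board. These soften the reporting gap substantially, but they do not settle which events enter the listing or which recording window applies.
- **The two statements on who grades can be reconciled** if the staff concerned are trained and authorised. Section 8.2 does promise training.
- **The operating procedure cited in 8.3.1 was not available for this review.** It may settle practice, but the protocol should not contradict itself.

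**Conclusion.** The contradiction is in the current text and survives these objections. Section 8.3.1 defines an adverse event both with and without a relatedness condition, and the conditional version conflicts with 8.3.4. Its serious-event bullet also differs from 8.3.2 on hospitalization and congenital anomaly.

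The consequence is conditional: if staff follow the narrow line, events judged unrelated to participation could be missing from the listing and from the committee's review. The number cannot be estimated, since the documents give no event rates for the 848 planned participants. The effect is confined to a descriptive safety record, the recording window and the reporting trigger. No hypothesis test, efficacy estimate or power figure changes. It is a modest inconsistency that is inexpensive to correct.

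**What to change.** Reconcile 8.3.1 with 8.3.2 and 8.3.4:

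- remove the condition of relatedness to participation from the adverse event definition, both in the study team's sentence and in the bullet;
- replace the serious-event bullet in 8.3.1 with a cross-reference to 8.3.2;
- state in 8.3.3.2 that relatedness is recorded after the event has been captured, by the trained and authorised persons described in 8.3.4;
- bring the cited operating procedure on adverse events into line;
- state in the SAP that any by-arm adverse event counts will be shown per person-time or over a common window, such as the first 6 months.

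The cost is wording in the protocol, the SAP and one operating procedure, and more event forms to complete. The last item is needed because broad capture makes raw counts depend on the unequal planned time on study.

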### 8.3.2 DEFINITION OF SERIOUS ADVERSE EVENTS (SAE)

An adverse event (AE) or suspected adverse reaction is considered "serious" if, in the view of either the investigator or sponsor, it results in any of the following outcomes: death, a life-threatening adverse event, inpatient hospitalization or prolongation of existing hospitalization, a persistent or significant incapacity or substantial disruption of the ability to conduct normal life functions, or a congenital anomaly/birth defect. Important medical events that may not result in death, be life-threatening, or require hospitalization may be considered serious when, based upon appropriate medical judgment, they may jeopardize the participant and may require medical or surgical intervention to prevent one of the outcomes listed in this definition. Examples of such medical events include allergic bronchospasm requiring intensive treatment in an emergency room or at home, blood dyscrasias or convulsions that do not result in inpatient hospitalization, or the development of drug dependency or drug abuse.

---

### 8.3.3 CLASSIFICATION OF AN ADVERSE EVENT

---

#### 8.3.3.1 SEVERITY OF EVENT

The study will also align its protocols with the standard definition of the AEs by severity of the situation or event.

- **Mild** – Events require minimal or no treatment and do not interfere with the participant's daily activities.
- **Moderate** – Events result in a low level of inconvenience or concern with therapeutic measures. Moderate events may cause some interference with functioning.
- **Severe** – Events interrupt a participant's usual daily activity and may require systemic drug therapy or other treatment. Severe events are usually potentially life-threatening or incapacitating. Of note, the term "severe" does not necessarily equate to "serious".

---

#### 8.3.3.2 RELATIONSHIP TO STUDY INTERVENTION

All AEs must have their relationship to study intervention assessed by the team member who conducted the intervention activities with the participant based on temporal relationship and staff judgment. The

degree of certainty about causality will be graded using the categories below. In a clinical trial, the study product must always be suspect.

- **Related** – The AE is known to occur with the study intervention, there is a reasonable possibility that the study intervention caused the AE, or there is a temporal relationship between the study intervention and event. Reasonable possibility means that there is evidence to suggest a causal relationship between the study intervention and the AE.
- **Not Related** – There is not a reasonable possibility that the administration of the study intervention caused the event, there is no temporal relationship between the study intervention and event onset, or an alternate etiology has been established.

---

#### 8.3.3.3 EXPECTEDNESS

The Data Safety and Monitoring Committee (DSMC) of the study will also be responsible for determining whether an AE is expected or unexpected. An AE will be considered unexpected if the nature, severity, or frequency of the event is not consistent with the risk information previously described for the study intervention.

---

#### 8.3.4. TIME PERIOD AND FREQUENCY FOR EVENT ASSESSMENT AND FOLLOW-UP

The occurrence of an AE or SAE may come to the attention of study staff during study visits and interviews of a study participant or upon review by a study monitor. All AEs that do not meet the criteria for SAEs will be captured on the appropriate case report form (CRF). Information to be collected includes event description, time of onset, staff or expert's assessment of severity, relationship to study intervention (assessed only by those with the training and authority to make a decision), and time of resolution/stabilization of the event. All AEs occurring while on study must be documented appropriately regardless of relationship. The study manager will record all reportable events with start dates occurring any time after informed consent is obtained until 7 (for non-serious AEs) or 30 days (for SAEs) after the last day of study participation. At each study visit, the PI will inquire about the occurrence of AE/SAEs since the last visit. All AEs will be followed to adequate resolution (**SOP Adverse Events and Unanticipated Problems**).

The Point of Care Artificial Intelligence DR screening procedure presents minimal risk to participants and the RAs will emphasize that it is specifically for diabetic retinopathy, not a substitute for a full eye examination. Examples of anticipated AE and AE response.

- If a participant shows signs of depression, stress, or anxiety, the staff will approach each situation with caution. This includes being attentive during consent, baseline survey, or screening processes that might emotionally affect the participant. In such cases, the staff will offer the participant a break, provide tissues or water, and inform them of the remaining tasks, asking if they would like to continue or need a break.
- If a participant shows signs of syncope or near syncope, the staff will assist the participant to either sit with their head between their knees or recline, if possible, use smelling salts, if necessary, provide a basin and towel if the participant is feeling nauseous, and ensure the participant remains seated until recovery. The study coordinator will be notified and decide whether the participant should continue with study activities or if medical intervention is needed.

---

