**The overall DRES-POCAI study will be considered complete** when participants' recruitment, all follow-up activities (including screenings and surveys) have been finalized, and the collected data has been cleaned, verified, and is ready for analysis. Participants assigned to the usual care group are anticipated to complete their participation within a six-month timeframe, and participants assigned to the intervention group are anticipated to complete the study's research activities at the 12 months from the initial study visit.

Participants may end their participation at any point of the intervention without completing the research activities in the following circumstances:

**Withdrawal:** Refers to participants who voluntarily decide to discontinue their involvement in the study before its completion.

**Lost to Follow-up:** Refers when participants fail to attend scheduled follow-up screenings, and /or are unreachable despite a defined number of contact attempts as defined in the protocols.

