#### 6.1.1 STUDY INTERVENTION DESCRIPTION

The purpose of the DRES-POCAI research study is to improve eye care by using a special camera and a computer system called EyeArt® to make diabetic eye screenings faster and more accessible. Eligible participants that choose to participate will complete a survey about diabetes management and eye health. They will also be randomized and assigned to one of the two study groups: usual care (receive a retinal screening by an eye care provider) or intervention group (receive a retinal screening using a special camera and EyeArt®). The study visit (baseline) is expected to be completed in a period of ~60 minutes.

During the first study visit, participants will:

1. Complete informed consent
2. Fill out a survey on diabetes, eye health, and barriers to retinal screening completion.
3. Undergo randomization and be assigned to a study group: usual care or intervention.
4. Undergo DR Screening. *Intervention group* participants will complete the DR screening using a special camera and the artificial intelligence (AI) system (EyeArt®) on the same day of the study

visit. Participants will also complete a satisfaction survey related to the use of EyeArt system to complete their DR screening.

*\*\*Usual care group* participants will complete the DR screening with an eye care provider on a different day and at a different location. The study staff will assist in scheduling appointments for the DR screening to ensure the completion of this important component.

5. Health Education Overview and Engagement materials: at the end of the study visit, the study staff will provide participants with an overview of the health education sessions. Staff will also ensure participants have scheduled any/all follow-ups. Participants will receive educational materials about diabetes care and management, eye health, etc.

Complete medical visit: Participants will complete a medical visit on the same day as the study visit (for in-person visits). If the medical visit is via telehealth, then participants will complete it on a different day after the screening.

Follow up contact with participants: After the first (baseline) study visit, all participants will participate in one 20-minute educational session and complete a short survey within 6 months of the baseline. Upon the completion of the second health education session and the 6-month follow-up survey, participants will receive a \$25 gift card.

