#### 10.1.5 SAFETY OVERSIGHT

Safety oversight will be under the direction of a Data and Safety Monitoring Committee (DSMC) composed of individuals with the appropriate expertise, including faculty from academic institution (i.e., San Diego State University) that are leaders of federally funded research projects, SYHealth medical expert with experience clinical research, member of the quality department with expertise in risk management, member of the quality analytics team, and the coordinator of the SYHealth Research Review Committee with extensive experience in Ethical and Responsible Conduct of Research and Human Subjects Protection program at SYHealth. Members of the DSMC are independent from the study conduct and free of conflict of interest, in addition, measures will be in place to minimize perceived conflict of interest. The DSMC will meet at least semiannually to assess safety and efficacy data on each arm of the study. The DSMC will operate under the rules of an approved protocol that will be written and reviewed at the organizational meeting of the DSMC. At this time, each data element that the DSMC needs to assess will be clearly defined. The purpose of the DSMC of the DRES-POCAI study will be to 1) periodically review and evaluate the accumulated study data for participant safety, study conduct and progress and efficacy, 2) assess all adverse events reported during the course of the study and 3) make recommendations concerning the continuation, modification, or termination of the study. The DSMC will consider study-specific data as well as relevant background knowledge about the disease, intervention, or target population under study.

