**Data Sources:** Data will be collected from a variety of sources:

- Participant Surveys: Baseline and follow-up surveys will be administered via EPIC-Research through MyChart (self-administered) or in paper format, if necessary.
- Electronic Health Records (EHR): Patient-level data including demographics, clinical data, DR screening results, referrals, diagnoses, and other relevant health measures will be extracted from the EHR.
- EyeArt® Point-of-Care AI System: Data from the POC-AI system (screening results, images, time metrics) will be collected.

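### Adverse-event recording runs up to about twice as long in the AI arm, and no AE question is specified for the contacts that follow the off-site usual-care exam, so crude by-arm AE data are not comparable

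*Combined protocol and SAP*

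**What the plan says.** **Window.** Protocol section 8.3.4 starts recording at consent and stops 7 days (non-serious AEs) or 30 days (SAEs) after the last day of participation. Section 4.4 sets that day by arm: "Participants assigned to the usual care group are anticipated to complete their participation within a six-month timeframe", while the AI arm is expected to finish 12 months after the initial visit. The same section limits the one-year repeat screen to AI participants whose first screen was negative. The synopsis gives a participant duration of one year without naming an arm.

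**Inquiry.** Section 8.3.4 says "At each study visit, the PI will inquire about the occurrence of AE/SAEs since the last visit". It also says that an event "may come to the attention of study staff during study visits and interviews of a study participant or upon review by a study monitor".

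**Where the screening happens.** The AI screen is done at the study visit. Under section 6.1.1, usual-care "participants will complete the DR screening with an eye care provider on a different day and at a different location". Sections 2.3.3 and 8.2 say that only usual care is dilated.

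**Later contacts, both arms.** Section 4.4 and the Schedule of Activities give three health education sessions within 6 months; section 6.1.1 gives one session and a short survey. Section 7.3 lets sessions be held by telephone or online and names them separately from a required study visit. On the surveys, section 10.1.7.1 says "Baseline and follow-up surveys will be administered via EPIC-Research through MyChart (self-administered) or in paper format, if necessary". The Schedule of Activities has no AE row.

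**Definition.** Section 8.3.1 cites the FDA definition, which does not depend on relatedness, and then adds the study team's own: "any unfavorable medical occurrence in a subject related to research participation, including signs, symptoms, or diseases". Section 8.3.4 says "All AEs occurring while on study must be documented appropriately regardless of relationship".

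**Use.** Section 10.1.5 says "The DSMC will meet at least semiannually to assess safety and efficacy data on each arm of the study". Protocol section 9.4.4 and the SAP's safety paragraph plan no safety endpoint, only presentation of the recorded events.

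**The concern.** Two features of the plan make AE capture depend on the arm.

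First, the recording window is tied to a last day of participation that differs by arm. With the same true event rate in both arms, the arm followed longer accumulates more events. No common window or person-time denominator is stated.

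Second, the arms are observed differently around the procedure itself. Staff are present at the AI screen, and section 8.2 tells them to track participants who decline or withdraw because of discomfort from it. The usual-care exam, the only one with dilation, happens away from study staff, and the text sets no counterpart for it. Whether anyone asks about it afterwards depends on whether the education contacts and the 6-month survey carry an AE question. The documents do not say. The survey domains listed in section 8.1 contain no AE item.

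The definition adds to this. If only events related to participation count, what is recorded depends on a judgement of relatedness, which section 8.3.3.2 gives to the team member who carried out the intervention activities. No study team member carries out the usual-care exam.

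At stake is how by-arm safety data are read. The DSMC may recommend that the trial continue, change or stop, and section 8.3.3.3 makes frequency one of the grounds for calling an event unexpected.

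**Working it through.** **Inputs**
- Participation: 6 months usual care, 12 months AI arm (section 4.4).
- Tail: 7 days for non-serious AEs, 30 days for SAEs (section 8.3.4).
- 424 participants per arm (section 5.1).
- One month = 365.25/12 = 30.44 days, so 6 months = 182.6 days and 12 months = 365.2 days.
- Assumed, not in the documents: the share p of AI participants with a negative first screen, and the event rate.

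**Step 1. All AI participants stay 12 months.** Window = participation + tail.
- Without the tail: 365.2/182.6 = 2.00.
- Non-serious AEs: (365.2 + 7)/(182.6 + 7) = 372.2/189.6 = 1.96.
- SAEs: (365.2 + 30)/(182.6 + 30) = 395.2/212.6 = 1.86.

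**Step 2. Only screen-negatives stay 12 months.** AI participants with any other result are assumed to end at 6 months, like usual care. Mean ratio = [p × AI window + (1 − p) × usual-care window] / usual-care window = 1 + p × 182.6 / usual-care window.

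| p (assumed) | Non-serious AEs | SAEs |
|---|---|---|
| 60% | 1.58 | 1.51 |
| 80% | 1.77 | 1.69 |
| 95% | 1.92 | 1.82 |
| 100% (step 1) | 1.96 | 1.86 |

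**Step 3. What this does to counts.** Take the same constant event rate r per year in both arms, all AI participants followed 12 months. Expected participants with at least one non-serious AE = 424 × [1 − exp(−r × window/365.25)].
- r = 2%: 4.4 usual care, 8.6 AI arm; apparent risk ratio 1.95.
- r = 20%: 41.8 usual care, 78.2 AI arm; apparent risk ratio 1.87.

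The true ratio is 1 in both rows.

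**Step 4. With a common window.** Consent to 6 months plus the same tail gives 189.6/189.6 = 1.00 for non-serious AEs and 212.6/212.6 = 1.00 for SAEs.

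**Step 5. Inquiry.** No arithmetic applies. Section 8.3.4 attaches the routine question to study visits. Section 4.4 calls the education contacts visits, while section 7.3 names them apart from a required study visit. So the text does not settle whether the routine question reaches either arm at those contacts.

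**The case against.** The case against has real force on several points, and they limit what can be claimed.

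- A reader might infer that AEs are picked up only at study visits. Section 8.3.4 also names participant interviews and monitor review, and section 8.2 describes continuous safety monitoring. Only the routine inquiry is tied to visits.
- A reader might infer that usual-care participants have no study visit after their exam. That is not established: education contacts and a 6-month survey are planned for everyone. Contact scripts may also stand in the AE procedure document, which is cited but not among the documents reviewed.
- A reader might take the AI arm to be watched exactly twice as long. The repeat screen is for screen-negatives only, so 1.96 and 1.86 are upper bounds.
- A reader might conclude that dilation reactions will be missed or that off-site events will go unrecorded. Usual-care results enter the medical record, EHR data are extracted, and section 8.3.4 requires recording whatever the relationship. Capture may be weaker; loss is not shown.
- No formal safety comparison is planned, events are listed with dates, the study is described as minimal risk, and the DSMC's own protocol, still to be written, will define the data it reviews.

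These points remove the stronger readings. They do not remove the unequal window, which follows from applying sections 4.4 and 8.3.4 as written, or the silence about the later contacts. A dated listing allows hand separation of late events, but nothing instructs anyone to do it.

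**Conclusion.** The point holds as a matter of comparability. As written, the AE window is longer in the AI arm by a factor of up to 1.96 (non-serious) or 1.86 (SAE), and about 1.6 to 1.9 or 1.5 to 1.8 if 60% to 95% of AI participants are screen-negative and the rest end at 6 months. That share is an assumption. Counts inflate by the same factor only if events arise at a constant rate; if they cluster around the screening, the longer window matters less and the difference in observation matters more. The size of that second effect cannot be calculated from the documents.

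The calculation also takes section 4.4 at its word. If the synopsis duration of one year applied to both arms, the windows would be equal, so those two passages need reconciling.

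The consequence is moderate. The primary and secondary analyses and the sample size are untouched. What is affected is the DSMC's by-arm review and any reader of the final AE table who compares the arms. The change is worth making because it is cheap and because a stated rule, not merely a missing detail, produces the imbalance.

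**What to change.** 1. In section 8.3.4 and the Schedule of Activities, put the same scripted AE/SAE question to both arms at the education contacts and the 6-month contact, however delivered. Reconcile the number of education sessions (three in section 4.4 and the Schedule, one in section 6.1.1), since the question depends on them.
2. In section 9.4.4 and the SAP's safety paragraph, tabulate AEs by arm for the DSMC and the final report over a common window, from consent to 6 months plus the same 7- or 30-day tail, or per person-time. List later AI-arm events separately. The common window is the safer choice if events cluster early, because dividing by longer follow-up would then favour the AI arm.
3. Reconcile the two AE definitions in section 8.3.1 with each other and with the recording rule in section 8.3.4. A rule that does not depend on relatedness keeps attribution out of the between-arm comparison.
4. Reconcile the one-year participant duration in the synopsis with the arm-specific durations in section 4.4.

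Cost: one added question at contacts already planned, edits to a few paragraphs, and a few more minor events to log. Endpoints and sample size do not change. A difference in observation on the day of the procedure will remain, because staff are present for only one of the two exams, but most of the imbalance is removed.
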